#### Secondary outcome—Paediatricians’ knowledge and practice gaps

We will assess the existence and potential change in paediatricians’ knowledge and practice gaps regarding EOS incidence, biomarker use and blood cultures.

### Data collection and data sources

To assess outcomes, quantitative and qualitative methods will be used. The main data sources are the EHRs, surveys, focus group evaluation sessions, an implementation logbook and field notes.

#### Data from the electronic health record

Data will be collected using automated data extraction methods of the hospitals’ business intelligence unit. Data will be sampled from all neonates with suspected EOS who were started on antibiotics during the pre- and post implementation period and include gestational age, birth weight, initiation of antibiotic treatment within the first 3 days of life, names and dosages of antibiotics used, duration of antibiotic treatment, blood culture results with pathogen identification, CRP and procalcitonin values within the first 28 days of life, readmissions within 28 days after discharge, re-initiation of antibiotic therapy within 28 days and discharge destination (home or transfer to another hospital). Additionally, the total number of live births during both periods will be obtained from hospital registries. All data will be securely stored in the Castor Electronic Data Capture (EDC) system.

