### Study setting and population

The study is conducted at the paediatric or specialised neonatal departments of 11 Dutch secondary hospitals and their surrounding primary neonatal care networks, consisting of obstetric practices and maternity care services. In the Netherlands, neonates at risk for EOS are initially managed either in obstetric wards (Level I) or neonatal wards (Levels II–IV), depending on their age and clinical condition. Most late-preterm and term neonates receive care in secondary hospitals (Level I–II facilities). Following discharge, continuity of care is provided by midwives, maternity nurses and general practitioners. Midwives hold medical responsibility for the mother and clinically well-appearing neonates during the first 10 days postpartum, with support from maternity nurses in the home setting. In cases where neonates continue oral antibiotic therapy at home, medical responsibility remains with the paediatrician, while supported by primary care.

Participating sites were purposively sampled covering various Dutch regions to create a proper reflection of region-bounded differences in organisation of care. The study population is twofold: (1) neonates born at 34 weeks of gestation or later with suspected EOS that will receive care associated with the interventions and (2) paediatricians, paediatric residents, nurse practitioners, neonatal nurses, maternity nurses and parents who are the focus of the implementation strategies. Other involved professionals are pharmacists, microbiologists, midwives, gynaecologists and gynaecologic residents.

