### Evidence-based antibiotic stewardship interventions

#### EOS calculator

The EOS calculator, which was developed by researchers of Kaiser Permanente, is applicable to neonates born at 34 weeks of gestation or later and can be used within the first 24 hours after birth.^10^ In this implementation project, it is advised to apply the EOS calculator to all neonates with increased risk of EOS, based on the presence of at least one risk factor or clinical symptom as specified in the current Dutch Society of Paediatrics’ guideline ‘Prevention and treatment of early onset neonatal infections’.^21^ The EOS calculator uses information on regional incidence and five maternal factors combined with the clinical evaluation of the neonate to assess individual EOS risk. The calculator then provides recommendations on the need for clinical observation using repeated evaluation of vital parameters, a blood culture and start of empirical intravenous antibiotics. In line with the protocol of the Dutch randomised controlled trial on EOS calculator safety and effectiveness, some deviations or clarifications have been made to the original EOS calculator’s approach in this study’s clinical protocol.^29^ First, the EOS calculator’s recommendation to obtain a blood culture and perform clinical observations is replaced with clinical observations only. This deviation reflects usual practices in the Netherlands, where obtaining a blood culture without subsequent antibiotic administration is uncommon. Second, evaluation of vital parameters is done every 3 hours instead of 4 hours, according to current Dutch workflows. Third, the EOS calculator gives no specific timeframe for observations in the ‘routine vitals’ recommendation, which is up to own interpretation. In this study’s clinical protocol, the duration has been standardised at 24 hours. For this implementation project, the EOS calculator is chosen over a 48-hour serial clinical examination approach, that also has the potential to significantly reduce antibiotic prescriptions, but demands more resources.^30^ The decision was based on the EOS calculator’s stronger evidence for reducing unnecessary antibiotic use, as well as logistical considerations regarding the demand for more staff and room capacity due to longer duration of the observation period of serial clinical examinations.

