#### Secondary implementation outcomes—antibiotic stewardship interventions

We will determine the adoption of the three antibiotic stewardship interventions on department level. The fidelity to the antibiotic stewardship strategies will be determined on patient level, by calculating the proportion of eligible patients in which the intervention was applied. Professionals’ reported feasibility and acceptability of the interventions will be assessed to understand levels of adoption and fidelity and to inform possible future refinements of the interventions.

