#### Secondary outcomes—clinical

We will determine the proportion of neonates starting on antibiotics per 100 live births, proportion of neonates receiving antibiotics per predefined category of duration (36 hours, 36–48 hours, 48–72 hours, >5 days and >7 days), duration of therapy, proportion of neonates receiving IV-to-oral switch therapy, duration of hospital stay, cumulative number of laboratory tests, cumulative readmission rate within 28 days after birth, cumulative bacterial (re)infection rate within 28 days after birth, incidence of culture-proven EOS per 1000 live births, pathogen determination and antibiotic susceptibility and infection-related mortality within 28 days after birth. For all (re)infections, we will provide exact data on timing of the infection within the first 28 days as well as the pathogen determination.

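### Patient-level data are extracted only for neonates started on antibiotics, so the 28-day safety outcomes omit neonates who stay untreated after the EOS calculator

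*Protocol article*

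**What the plan says.** The section on electronic health record data sets the sampling frame: "Data will be sampled from all neonates with suspected EOS who were started on antibiotics during the pre- and post implementation period". The one item outside that frame is an aggregate: "the total number of live births during both periods will be obtained from hospital registries". None of the other sources described (surveys, focus groups, interviews, logbook, field notes) is set up to supply clinical outcomes for individual untreated neonates.

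Three other places use a wider group:

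- **Study setting and population:** the neonatal population is "neonates born at 34 weeks of gestation or later with suspected EOS that will receive care associated with the interventions", with no condition that treatment was started.
- **EOS calculator:** "it is advised to apply the EOS calculator to all neonates with increased risk of EOS", which comes before any decision to treat.
- **Secondary clinical outcomes:** the list includes "cumulative readmission rate within 28 days after birth, cumulative bacterial (re)infection rate within 28 days after birth" and "infection-related mortality within 28 days after birth", again without restriction to treated neonates.

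Fidelity to the interventions is to be measured on patient level "by calculating the proportion of eligible patients in which the intervention was applied". The extracted follow-up items are "readmissions within 28 days after discharge, re-initiation of antibiotic therapy within 28 days".

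**The concern.** The frame is conditioned on something the intervention changes. The calculator is applied to at-risk neonates, and some who would have been treated before are then observed without antibiotics. If such a neonate stays untreated and is readmitted, or has a later infection or dies without having been started on treatment for suspected EOS, the event is not in the dataset. The neonates who do start antibiotics after implementation are fewer and probably at higher risk than those who started before.

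What is at stake is the meaning of the 28-day results. They would be read as evidence on the safety of the bundle in routine care, yet they would not cover neonates spared antibiotics. They could also move in either direction with no change in any neonate's risk.

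Calculator fidelity has the same gap. Its eligible group includes neonates who remain untreated, and they are not in the extract.

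**Working it through.** **Inputs, all from the protocol article.** 11 hospitals (Study setting). From Sample size: initiation rate 3.8% of live births before and 2% as the goal after; about 2,500 births per hospital per year, range 1,000 to 3,500. From the Introduction: up to 44% fewer prescriptions with the calculator.

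**Step 1: reproduce the plan's figure that uses the 3.8%.** (0.685 × 38 × 2) + (0.315 × 38 × 7) = 52.06 + 83.79 = 135.85, which rounds to the stated 136 days on therapy per 1,000 live births. So 38 treated neonates per 1,000 births is the plan's own baseline.

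**Step 2: size of the extract in each period.** Births per year: 11 × 2,500 = 27,500.

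- Before: 27,500 × 0.038 = 1,045
- After, at the goal: 27,500 × 0.020 = 550
- Net difference: 495, which is 18 of every 38 formerly treated (47%)
- With 1,000 births per hospital: 11,000 × 0.018 = 198; with 3,500: 38,500 × 0.018 = 693
- With the 44% reduction instead of the goal: 1,045 × 0.44 = about 460
- If only the 10% reduction in days on therapy that the plan calls clinically relevant is reached, and all of it comes from fewer starts: 1,045 × 0.10 = about 105. If it comes only from shorter courses, the difference is nil.

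**Step 3: what this does to a pre/post rate.** The article gives no 28-day event risks. Purely as an assumption, let the 495 neonates no longer treated have a risk of 0.5% and the 550 still treated a risk of 5%, unchanged between periods. Count only events that are not preceded by a treatment start for suspected EOS in the 495.

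| | Before | After |
|---|---|---|
| Recorded events | 495 × 0.005 + 550 × 0.05 = 29.975 | 550 × 0.05 = 27.5 |
| Per treated neonate | 29.975 / 1,045 = 2.9% | 27.5 / 550 = 5.0% |
| Per 1,000 live births | 29.975 / 27.5 = 1.09 | 27.5 / 27.5 = 1.00 |

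The same neonates with the same risks give a rising rate on one denominator and a falling rate on the other. Changing the denominator does not repair the comparison, because the events of untreated neonates are missing from the numerator. If the risk in the 495 lay anywhere from 0.5% to 5%, about 2 to 25 events a year would go unrecorded (495 × 0.005 = 2.5; 495 × 0.05 = 24.75).

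**Step 4: the readmission window.** The outcome runs to 28 days after birth and the extracted item to 28 days after discharge. Discharge follows birth, so the extracted window always contains the outcome window. The outcome can be derived if readmission dates are kept.

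**The case against.** The strongest reply is that the primary aim is antibiotic exposure, which this frame serves fully. The affected outcomes are secondary, and the article treats the safety of the three interventions as already established. That stands, and it limits the weight of the point. It does not remove it: the article lists 28-day infection, readmission and mortality as outcomes, and justifies the study by the lack of evidence on how these interventions work and interact in routine care.

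A reader might infer more than the text supports:

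- **That neonates from whom the calculator withholds treatment are never seen.** Not so. One who is observed first and then started on antibiotics for suspected EOS at a participating site meets the sampling criterion. Culture-proven EOS, reported against live births, is therefore still largely counted. The calculator's recommendation is not among the listed items, however, so these neonates could not be identified as initially withheld.
- **That the only group at risk from the bundle is lost.** PCT-guided stopping and the oral switch act on treated neonates, who are in the extract.
- **That the safety rates will be calculated per treated neonate.** The article states no denominator for them. Outcome definitions are in supplementary table S5, which is not shown. Step 3 shows that the problem remains on either denominator.
- **That most at-risk neonates are missing from the fidelity calculation.** The article does not say how many go untreated.
- **That antibiotic start within three days is an inclusion rule.** It appears among the extracted items. The 72-hour limit belongs to the primary outcome.
- **That the two readmission windows conflict in a harmful way.** Step 4 shows that they do not.

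The count of 495 is also a net figure at an ambitious goal, with an average birth number applied to every site. It counts neonates, not events.

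**Conclusion.** The point holds in limited form. As written, the extract gives no 28-day readmission, later infection or infection-related death for neonates who stay untreated after the calculator. The pre/post comparison of these outcomes is therefore affected by selection and cannot show safety in neonates spared antibiotics. Patient-level calculator fidelity among all eligible neonates cannot be computed from this extract.

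At the plan's goal the net difference is about 495 neonates a year (198 to 693 over the stated range of births), and less if initiation falls less. This rests on 11 hospitals, the stated birth numbers and initiation rates, and the sampling sentence meaning what it says; table S5 could qualify the outcome definitions. The number of events lost cannot be derived from the article. The primary days-on-therapy analysis is not affected.

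**What to change.** For both periods, extend the automated query to all live births of at least 34 weeks at the participating hospitals, for a short list of dated events to day 28 after birth: readmission, positive blood or cerebrospinal fluid culture, any antibiotic start, and death. Report these per 1,000 live births of at least 34 weeks, using a birth count restricted in the same way, beside the results in treated neonates.

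Derive readmission within 28 days after birth from the dates, and use that window in both sections. Label calculator fidelity as fidelity among treated neonates unless at-risk neonates are also extracted; that would need risk-factor and symptom data, which are not among the listed items.

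**Cost.** The extract becomes much larger though shallow: at most about 27,500 records per period at the average birth number, against 1,045 and 550, or roughly 26 and 50 times as many. The committees that granted the consent waiver would need to be notified. No new visits are needed. Events at other hospitals would remain unseen and should be stated as a limitation. If the wider query is refused, the report should say plainly that the 28-day outcomes do not cover neonates who stayed untreated.

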#### Surveys

All paediatricians of the participating sites will be invited to complete a survey both before and 1 year after the active implementation period to assess changes in knowledge and practice gaps and the adoption of the interventions. Additionally, the post implementation survey will evaluate fidelity to and appropriateness of the implementation strategies 1–3 and 8 and assess acceptability and feasibility of the antibiotic stewardship interventions (onlinesupplemental files 4  5). Paediatric residents will only take part in the post implementation survey, as their frequent rotations across different workplaces make pre-implementation comparisons unfeasible. Neonatology nurses will also be invited to complete a survey, specifically to assess the acceptability and feasibility of IV-to-oral switch therapy and the fidelity to and appropriateness of strategies 1, 6 and 7 (online supplemental file 6). All surveys will be distributed via the Castor EDC system.

#### Focus group evaluation sessions

Focus group evaluation sessions with paediatricians, paediatric residents and nurse practitioners will be conducted at each site, 9–12 months after the implementation period was completed. The sessions will include 6–12 participants and have a duration of approximately 60 min. To ensure a sample that is as representative as possible, all focus groups will be conducted during regularly scheduled ward meetings during working hours, typically attended by all physicians on duty. These meetings naturally include a diverse group of individuals with varying roles and expertise within the department. Those expected to be on duty on the day of the focus group will be invited to participate by the local champions. Participants’ gender, professional role and years of working experience in their role will be recorded. The sessions will follow a semi-structured format, allowing the interviewer to explore qualitative insights into the implementation process and the antibiotic stewardship interventions (online supplemental file 7). All sessions will be audio-recorded, transcribed verbatim and securely stored on a departmental disk. Participant anonymity will be ensured by removing identifying information from the transcripts.

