### Implementation strategies

#### Strategy 1: Appointment of local implementation team and task list

Per site, an implementation team will be appointed, consisting of at least one nurse champion and two paediatrician champions (early adopters) that are tasked with leading implementation of the interventions within their hospital and its associated neonatal care network. The appointed implementation champions are respected individuals within the organisation who have the ability to motivate and engage their colleagues and have positive attitudes regarding the interventions. The implementation team will be briefed by the central study team and will be provided with a list of tasks and responsibilities. First, they will work towards their department’s adoption of the antibiotic stewardship interventions by (1) briefing and discussing the interventions with the paediatric specialist group and microbiologist, (2) reviewing resource availability with the clinical chemistry laboratory (PCT determination equipment) and pharmacy (amoxicillin suspension), (3) informing and engaging the obstetric department and obstetric partnerships and (4) adapting local medical and nursing guidelines to incorporate the interventions. Second, the implementation team supports implementation during the entire rollout of the project, by sharing their knowledge, reminding colleagues to adhere to the interventions and serving as primary point of contact for colleagues. To assist the local champions in discussing availability of resources and engaging stakeholders, the central research team provides tailored scientific information on PCT costs and IV-to-oral switch therapy, as well as a fact sheet with information about the intervention for the obstetric partnerships, if required. Moreover, the protocols of the antibiotic stewardship intervention will be made available in separate modules by the central research team, to facilitate integration of the interventions in the local protocol independently of each other.

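### Champions chosen partly for favourable views issue the focus-group invitations and may take part, and champion status is not listed as recorded, so a favourable tilt in the implementation findings could not be examined

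*Protocol article*

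**What the plan says.** Under Strategy 1, each site has an implementation team "consisting of at least one nurse champion and two paediatrician champions (early adopters"). Members are selected as people who "have the ability to motivate and engage their colleagues and have positive attitudes regarding the interventions". They lead implementation locally and remind colleagues to adhere.

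Under Focus group evaluation sessions, meetings with paediatricians, residents and nurse practitioners are held at every site. On size: "The sessions will include 6–12 participants and have a duration of approximately 60 min". On recruitment: "Those expected to be on duty on the day of the focus group will be invited to participate by the local champions". As a safeguard for representativeness, "all focus groups will be conducted during regularly scheduled ward meetings during working hours, typically attended by all physicians on duty". On participant data: "gender, professional role and years of working experience in their role will be recorded". Transcripts are stripped of identifying information.

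Under Surveys, "All paediatricians of the participating sites will be invited to complete a survey" before implementation and one year after it. The later survey covers acceptability and feasibility of the interventions, and fidelity to and appropriateness of Strategies 1–3 and 8. Residents answer the later survey only. Neonatology nurses are surveyed on oral switch therapy and on Strategies 1, 6 and 7. All surveys go out through the electronic data capture system.

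**The concern.** Acceptability, feasibility and appropriateness are stated secondary aims, meant to explain uptake and to guide refinement. They are useful to other hospitals to the extent that they reflect ordinary staff.

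The plan gives champions two roles at once. They are picked partly because they already favour the interventions and are made responsible for local success. They then invite colleagues to the session that evaluates the interventions and the strategies, and may sit in it. Two mechanisms could make the findings more favourable: champions' own views enter the data, and colleagues may speak less critically when invited by, or sitting beside, the person who reminds them to adhere. In the survey, champions can rate the usefulness of appointing champions.

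If champion status is not captured at the session, anonymised transcripts may not allow the two groups to be told apart later.

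**Working it through.** The plan states no figure on this point, so there is nothing to reproduce. The check sets the sections side by side, with one small calculation for scale.

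**Source by source**

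| Source | Who invites or sends | Champions within the sample? | Champion status recorded? |
|---|---|---|---|
| Focus groups (qualitative) | Local champions, to those expected on duty | Not stated; no exclusion | Not among the listed items |
| Paediatrician survey | Electronic data capture system | Yes, as all paediatricians are invited | Items are in supplements not shown |
| Nurse survey | Electronic data capture system | Nurse champion, unless excluded | Items are in supplements not shown |
| Parent interviews | The family's paediatrician | Not applicable | Not applicable |
| Maternity-nurse interviews | Identified through obstetric partnerships and parents | Not applicable | Not applicable |

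Champion-led invitation is thus a feature of the focus groups only. Membership of the sample extends to the surveys. No section states a separate analysis of champions.

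**Share of a focus group**

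Inputs: at least 2 paediatrician champions per site (Strategy 1); 6–12 participants per session (Focus group evaluation sessions). Share = champions attending / participants.

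- Both attend: 2/12 = 17% to 2/6 = 33%.
- One attends: 1/12 = 8% to 1/6 = 17%.
- None attends: 0%, with only the invitation route left.

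Over 11 sites there are at least 2 × 11 = 22 paediatrician champions. The nurse champion is not in the focus-group population unless a nurse practitioner.

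**Survey**

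The shift in a mean rating would be (champion share) × (champion mean − non-champion mean). The document gives neither the number of paediatricians per site, nor response rates, nor any rating, so neither factor is known. Residents answering the same survey would lower the share.

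The planned summary for Likert items is the median with IQR, and a median need not move. Two invented five-point distributions show this, assuming a champion share of 17% with every champion scoring 5:

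- Non-champions 10/20/30/30/10%: cumulative share up to score 3 is 60%, so the median is 3. With champions it is 0.83 × 60% = 49.8%, so the median becomes 4.
- Non-champions 5/10/20/40/25%: cumulative share is 35% up to score 3 and 75% up to score 4, so the median is 4. With champions these become 29.1% and 62.3%, and the median stays 4.

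These examples show only that the effect on the planned summary can be a full point or nothing. They do not estimate the bias.

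**The case against.** The strongest reply is that focus-group attendance is set by the duty schedule and held at routine ward meetings, so the champion merely passes on an invitation. No text gives champions discretion over whom to ask, and none says they attend. This largely answers the worry about hand-picking. It does not prevent a champion on duty from attending, does not remove the social pressure of being invited by the local advocate, and does not make champion statements identifiable.

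A second reply is that the central team knows who the champions are, since it briefs the implementation teams and logs their tasks. That makes recording their status easy, but the listed participant data do not include it.

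A third is that champions are genuine members of the departments and key informants on the implementation process. That stands, and is a reason not to exclude them.

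A reader might infer more: that the acceptability and feasibility ratings are inflated by a definite amount and that champions' answers can never be separated. The document does not support this. The structured ratings come from surveys that champions are not said to send, and the survey items are in supplements not shown, so a champion item may exist. Any numerical inflation would rest wholly on assumed site sizes, response rates and rating gaps.

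**Conclusion.** The point holds as a risk, mainly for the qualitative focus-group findings. People selected partly for favourable views issue the invitations, may be present, and cannot be distinguished on the listed participant data. The survey ratings share the risk to a lesser extent, most directly where appropriateness of Strategy 1 is rated, but its size cannot be determined.

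The only scale the document supports is the possible champion share of a focus group: 8–17% with one attending and 17–33% with two, at the stated minimum of two paediatrician champions. This rests on the assumption, not stated in the plan, that champions attend. Bias is possible rather than shown. Only secondary implementation outcomes are concerned; the primary outcome, days on therapy per 1000 live births, is untouched.

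**What to change.** 1. Have the central team send the focus-group invitations from the duty roster.
2. Record champion status (yes/no) for each focus-group participant, and carry it as a non-identifying label into the transcript.
3. Confirm that the staff surveys contain a champion item; add one if they do not.
4. Report acceptability, feasibility and appropriateness for all respondents, and again without champions as a sensitivity analysis. In the qualitative synthesis, note whether a theme rests on champions alone.

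Champions need not be excluded, and the non-champion result need not become the main figure: that would give up information on the implementation process.

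The cost is one data item, a little more analysis and a small extra task for the central team. Status is best captured at the session, because it may not be recoverable from anonymised transcripts.
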